## Abstract

**Background:** During the menopausal transition, women often experience physical (e.g., vasomotor symptoms) and emotional (e.g., anxiety and depression) difficulties that significantly impact functioning and overall quality of life. Although sexual concerns (e.g., decreased sexual desire, orgasm), are reported by up to 87% of peri- and post-menopausal women, and are associated with adverse impact on functioning and distress, treatment options that directly target this area are limited, and most often involve medication (e.g., hormone replacement). Effectiveness of these treatments is often defined as improvements in physical symptoms, however, associated psychological and emotional symptoms rarely, if at all, improve. Cognitive behavioral therapy (CBT) has been proposed as a low-risk treatment for menopausal symptoms with studies showing improvement in frequently reported symptoms (e.g., vasomotor symptoms, depression, anxiety, sleep). Sexual concerns, however, have either not been directly targeted at all in current CBT protocols, or the very few protocols that include sexual concerns, demonstrated modest gains in sexual desire.

**Methods:** This protocol paper outlines the development, design, and implementation of a newly developed CBT for sexual concerns trial during perimenopause (CBT-SC-Peri). Although sexual concerns are prevalent during both the peri- and post-menopausal periods, we will be evaluating the effectiveness of a CBT-SC protocol specifically for perimenopausal women as a means of early intervention. The clinical sample will comprise 82 women aged 40–60 years currently in perimenopause, as per the Stages of Reproductive Aging Workshop (STRAW) definition, and medication stable (if applicable). To ensure participants are experiencing clinically significant sexual concerns, a baseline cut-off score of 26 or lower on the Female Sexual Functioning Index will be utilized. Exclusion criteria include participants with psychotic disorders, or current substance and/or alcohol dependence, or severely depressed/suicidal. The CBT-SC-Peri is a weekly, four session treatment, lasting up to 90 min per session and includes psychoeducation and cognitive and behavioral strategies designed to challenge unhelpful beliefs and promote healthy sexual behaviors. As this is an individual CBT protocol, content will be tailored to address the specific problems relevant for each participant. Eligible women will be placed directly into treatment or on a 4-week waitlist and reassessed prior to starting treatment. The primary outcome (sexual satisfaction), as well as secondary outcomes (desire, arousal, relationship satisfaction, body image, vasomotor symptoms, depression, and anxiety) are assessed at baseline, post-waitlist (for those on waitlist), and post-treatment.

**Discussion:** To our knowledge, this will be the first study to investigate the efficacy of a CBT protocol (CBT-SC-Peri) specifically aimed at improving sexual concerns experienced during perimenopause. If effective, this form of treatment may not only be preferred by some, but necessary for others as consumer demand increases for non-pharmacological treatments for perimenopausal symptoms. Further, this protocol can be integrated into perimenopausal care and will be made available by dissemination to healthcare practitioners.

**Clinical Trial Registration:** Trial # NCT04922385 and Accessible at: https://clinicaltrials.gov/ct2/show/NCT04922385?term=NCT04922385anddraw=2andrank=1.

## Introduction

The menopausal transition is often accompanied by adverse physical (e.g., vasomotor symptoms, sleep difficulties, sexual concerns) and emotional (e.g., anxiety, depression) changes that significantly impact a woman's functioning and overall quality of life (1–4). Sexual concerns are reported by as many as 68–86.5% of menopausal women (5) and yet have received little attention in the clinical literature. Commonly reported sexual concerns include decreased sexual desire, reduced ability to have an orgasm, and pain during intercourse. These sexual concerns may be due to decreases in estrogen levels leading to vulvovaginal atrophy (6), decreased elasticity of the vaginal walls, and decreased vascularization and innervation of vulvovaginal tissue (6). These physical changes can result in genital dryness and irritation, impaired perception of touch and vibration, and often dyspareunia, all contributing to a reduction in sexual satisfaction (7). Further, sexual concerns have been found to contribute to poor self-image, lower sense of sexual attractiveness, and can have a negative impact on physical and emotional well-being (8). Consistent with the World Health Organization's (9) definition of sexual health, sexual concerns exhibited during the menopausal transition are not just physical, but also psychological and emotional in nature. Despite the prevalence of sexual concerns, their impact on functioning and associated distress, treatment options that directly target this area of functioning among women going through the menopausal transition are limited.

The most commonly prescribed treatment for sexual concerns during the menopausal transition is hormone therapy (HT), which generally includes a combination of estrogen- and progesterone-based compounds (10, 11). For some women, HT may be associated with health risks, including an increased risk for cardiovascular events and breast cancer after long term use (12–14). Testosterone treatments have also been reported to improve sexual concerns during menopause, however, these treatments have also been associated with adverse side effects [e.g., higher incidence of hair growth, vaginal bleeding, weight gain, increased LDL-cholesterol; (13, 15)]. Further, effectiveness of these treatments is typically defined as improvements in physical symptoms, such as vaginal dryness, atrophy, and pain during intercourse. Psychological and emotional symptoms associated with sexual concerns during the menopausal transition (e.g., self-image, desire) are rarely, if at all, improved with these treatments (16).

Psychological therapy, specifically Cognitive Behavioral Therapy (CBT), has been proposed as a low-risk treatment for menopausal symptoms with studies showing CBT as effective in reducing several common menopausal symptoms [e.g., vasomotor symptoms, depression, anxiety, and sleep difficulties; (17–19)]. Sexual concerns, however, have either not been directly targeted at all in current CBT protocols, or the two protocols that have included sessions on sexual concerns (19, 20), have only demonstrated modest gains in a single domain (e.g., sexual desire). Further, most CBT studies for menopause have included broad measures of menopausal symptoms (e.g., the Greene Climacteric Scale, Menopause Rating Scale), which do not allow us to determine the impact of CBT on important domains of sexual functioning and satisfaction specifically sexual desire, interest, and self-image. As a result, it is still not known whether CBT for menopausal symptoms can improve a wide array of sexual concerns.

Given the high rates and associated impairment of sexual concerns during perimenopause, we developed a CBT protocol specifically designed to target sexual concerns during perimenopause as a means of early intervention. Although decline in sexual function and satisfaction naturally decreases with age (13), this decline may also significantly reduce quality of life. As a result, we aim to address sexual concerns earlier in the menopausal transition with the goal of both improving sexual satisfaction, as well as reducing the impact on one's quality of life to improve future outcomes. The primary objective of this study is to evaluate the efficacy of this weekly, four-session, individual CBT for sexual concerns in perimenopause (CBT-SC-Peri) protocol. It is hypothesized that the CBT-SC-Peri protocol will significantly improve sexual satisfaction (primary outcome), desire, arousal, relationship satisfaction, body image, vasomotor symptoms, depression, and anxiety (secondary outcomes). To our knowledge, this will be the first study to investigate the efficacy of a CBT protocol (CBT-SC-Peri) specifically aimed at improving sexual concerns and associated distress experienced during perimenopause. As consumer demand increases for non-pharmacological treatments for perimenopausal symptoms, this form of treatment may not only be preferred by some, but necessary for others as hormonal treatments commonly have associated adverse effects and/or are contraindicated for some women.

## Methods

### Participants

#### Inclusion/Exclusion Criteria

The clinical sample for this study will comprise participants who meet the following inclusion criteria: (1) 40–60 years of age, who are either single or have a partner; (2) peri-menopausal and have had a menstrual period within the previous 12 months as per the STRAW definition (21), (3) cut-off score of 26 or lower on the Female Sexual Functioning Index, indicating sexual dysfunction (22), (4) medication stable (e.g., HT), with no changes in dosing for the previous 3 months (19), (5) no psychological treatment to address sexual dysfunction and/or sexual concerns within the previous 6 months; and (6) speak, read, and write in English to comprehend testing procedures and written materials in treatment. Participants will be excluded if: (1) they have any psychotic disorders, or current substance and/or alcohol dependence; and/or (2) are severely depressed/suicidal at time of the intake assessment as they would not be able to meaningfully participant in treatment.

#### Sample Size

Based on our data from our CBT for menopausal symptoms randomized controlled trial (19), as well as in previous studies (20) assessing the efficacy of CBT for sexual concerns in menopausal women, we estimate a medium effect size of 0.5 for our study. Using an ANCOVA power analysis to calculate sample size, and with a level of significance set at α = 0.05 and a study power set at 80%, 68 participants are required to conduct our study. Adjusting our sample for a 20% attrition rate, we plan on recruiting 82 participants.

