### Statistical Analysis Plan

Treatment response will be determined using multiple measures, as identified in the assessment battery, and distinguished between primary and secondary efficacy analyses. A series of repeated measures analysis of covariance (ANCOVA) will be used to examine condition differences. A two (treatment vs. wait-list) by two (time: pre-treatment, post-treatment) repeated measures ANCOVA will be used to examine differences in both primary and secondary outcomes, specifically sexual satisfaction and desire, body image, partner satisfaction, vasomotor symptoms, as well as depression and anxiety symptoms. Covariates for all analyses will include age, current marital status, medication use at baseline, treatment delivery method, and baseline depression and anxiety severity. If continuous variables do not meet the assumptions of normality, as assessed by the Shapiro-Wilk test, we will use non-parametric methods, with alpha levels set at 0.05.

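### The stated inputs do not reproduce 68 participants: that total needs an unreported correlation of about 0.69–0.70, and the planned repeated measures test is not the ANCOVA that would use it

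*Protocol article*

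**What the plan says.** The Sample Size section of the protocol article gives these planning inputs:

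- Effect: "we estimate a medium effect size of 0.5 for our study", attributed to the team's earlier trial and to previous studies.
- Error rate and power: "with a level of significance set at α = 0.05" and 80% power.
- Method: "Using an ANCOVA power analysis to calculate sample size".
- Result: "study power set at 80%, 68 participants are required to conduct our study", followed by "Adjusting our sample for a 20% attrition rate, we plan on recruiting 82 participants".

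It does not say what correlation or explained variance was assumed, whether the test is one- or two-sided, what the group ratio is, or whether 0.5 is a standardised mean difference (d) or Cohen's f.

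The Statistical Analysis Plan section specifies a repeated measures ANCOVA with two conditions (treatment, waitlist) and two times (before and after). On adjustment it says: "Covariates for all analyses will include age, current marital status, medication use at baseline, treatment delivery method, and baseline depression and anxiety severity". The outcome's own baseline is not on that list; it enters the model only as the first level of the time factor. Under Study Design, a participant goes on the waitlist when no clinician is free, so the group sizes are not fixed.

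**The concern.** The section reads as a complete calculation, yet its printed inputs do not lead to its printed result. ANCOVA reduces a sample size only through the variance its covariates explain. That is the input that would bring 128 down to 68, and it is the one not given.

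The calculation and the planned test also do not visibly match. A gain computed for a baseline-adjusted ANCOVA does not transfer in full to a group-by-time test on two occasions.

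At stake is the meaning of the 80%. The recruitment target of 82 rests on 68. If the real correlation is moderate, a true effect of 0.5 would be missed more often than the stated 20%, and a null result could be over-read as evidence against the therapy.

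**Working it through.** **Inputs.** From Sample Size: effect 0.5, alpha 0.05, power 80%, 68 evaluable. Assumed here because not stated: 0.5 is d (medium on that scale; the equivalent f is 0.25), two-sided test, 34 per group. Equal groups are the most favourable case.

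**Step 1: try to reproduce 68 without a correlation.** Power comes from the non-central t with non-centrality d × √(n/2), n per group.

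| Reading of the stated inputs | Total N |
|---|---|
| d = 0.5, two-sided, 1:1 | 128 (64 per group, power 80.1%); 126 by normal approximation |
| d = 0.5, one-sided, 1:1 | 102 |
| ANCOVA F test, f = 0.25, 1 df, with 0, 1 or 6 covariates and no variance explained | 128 |
| 0.5 taken as f, 1 df | 34 |

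None gives 68. With 34 per group and no covariate gain, power for d = 0.5 is 53%, and 80% power is reached only at d of about 0.69.

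**Step 2: add a baseline covariate.** For an ANCOVA of the follow-up score on its own baseline with correlation r, the residual variance is multiplied by (1 − r²) and one further df is lost. The non-centrality becomes 0.5 × √17 / √(1 − r²).

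- Solving for 80% power at 34 per group gives r = 0.689, so r² is about 0.47. As a rough check, 1 − 68/128 = 0.469 and √0.469 = 0.685.
- At r = 0.69 or 0.70 the required total is 68; at 0.68 it is 70 and at 0.71 it is 66.
- One-sided, r = 0.572 is enough.

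So 68 can be obtained, but only with a value the article does not report.

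**Step 3: apply the analysis actually planned.** With two groups and two occasions, the group-by-time test is a t test on change scores. The variance of change is 2(1 − r) times the single-occasion variance, so the non-centrality is 0.5 × √17 / √(2(1 − r)). At r = 0.70 the factor is 0.60, against 1 − 0.49 = 0.51 for ANCOVA.

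| r | Power at 68, baseline-adjusted ANCOVA | Power at 68, change scores |
|---|---|---|
| 0.5 | 65% | 53% |
| 0.6 | 72% | 62% |
| 0.70 | 81% | 75% |

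The change-score test needs r of about 0.74 for 80% power at 68, or 78 participants at r = 0.70. These figures assume no further gain from the listed covariates.

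**Step 4: unequal groups.** With 68 split about 2:1 (45 and 23), the baseline-adjusted ANCOVA at r = 0.70 has about 77% power instead of 81%.

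**The case against.** The strongest reply is that the section names an ANCOVA calculation. The 128 is the total with zero covariate gain, which is not what ANCOVA planning normally assumes, and a round planning value of 0.7 returns exactly 68. That favours an unreported input over a mistake. A reader might infer from the gap between 128 and 68 that the sponsor miscalculated, or that the trial has only 53% power. The documents support neither: 68 is attainable under the named method, and 53% is the zero-gain extreme for ANCOVA, not a central estimate. The reply stands on both counts.

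It can also be said that a journal article may leave an assumed correlation to the full protocol, that a one-sided test would need only about 0.57, and that the earlier trial data might support 0.7. Whether they do cannot be judged from this document.

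Finally, the outcome's baseline is in the planned model, as a level of time. That is true, but it is what makes the test a change-score comparison. The mismatch therefore does not depend on the missing detail: the same r = 0.70 that yields 68 for a baseline-adjusted ANCOVA yields about 75% power under the model the article specifies.

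**Conclusion.** The point holds as a calculation that cannot be reproduced, and as a mismatch between the calculation and the planned test. It does not hold as a proven arithmetic error.

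The stated inputs alone give 128. The 68 follows only from a two-sided baseline-adjusted ANCOVA with r of about 0.69–0.70, or about 0.57 if one-sided. Under the repeated measures test as written, power at 68 is about 75% at r = 0.70, 62% at 0.6 and 53% at 0.5, and 80% needs about 0.74.

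This rests on reading 0.5 as d, a two-sided test, equal groups, equal variances at the two occasions and no further gain from the listed covariates. Further gain would raise these figures; unequal groups would lower them.

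**What to change.** 1. In Sample Size, state the assumed correlation and its source (the earlier trial data already cited there), the sidedness, the assumed group ratio, and that 0.5 is a standardised mean difference.
2. In Statistical Analysis Plan, make the primary analysis an ANCOVA of the second-assessment score (post-treatment against post-waitlist) with the outcome's own baseline as a covariate, replacing the time factor. Adding that baseline to the present model while keeping the time factor would use the same measurement twice.
3. If r of about 0.69 cannot be supported, restate what 68 completers provide under that ANCOVA: about 65–72% power for d = 0.5 at r = 0.5–0.6, 53% with no covariate gain, or 80% power for d of about 0.69 with no gain. Add that unequal groups lower this further (about 77% at 2:1 even with r = 0.70).

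The cost is a reworded Sample Size section, a change of model in the analysis section and possibly a less favourable stated power. No additional enrolment is required.

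### Allowing for 20% attrition turns 68 into 85 recruits, not 82; recruiting 82 leaves about 65 or 66 completers, below the stated requirement

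*Protocol article*

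**What the plan says.** The Sample Size section takes a medium effect size of 0.5, a significance level of 0.05 and 80% power, uses an ANCOVA power calculation, and concludes that "68 participants are required to conduct our study". The next sentence reads: "Adjusting our sample for a 20% attrition rate, we plan on recruiting 82 participants". The Methods part of the Abstract repeats the target: "The clinical sample will comprise 82 women". The article gives no other attrition rate and no other rule for getting from 68 to the recruitment target.

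**The concern.** An attrition allowance should ensure that the required number is still there for analysis after the expected losses. The losses come out of the recruited group, so the required number must be divided by the proportion retained. The step from 68 to 82 multiplies by 1.20 instead. The target then falls short of the required number under the plan's own attrition assumption, and the 80% power claimed for the trial is not delivered if that assumption comes true. The Discussion says the study could be the basis for a larger randomized trial, where the same inflation rule might be reused.

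**Working it through.** **Inputs (all from Sample Size; the 82 also appears in the Abstract)**

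- Required number, n = 68
- Attrition, a = 0.20
- Recruitment target, N = 82

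**Reproducing the plan's figure**

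n × (1 + a) = 68 × 1.20 = 81.6, rounded up to 82. This matches the plan.

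**Correct inflation**

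n / (1 − a) = 68 / 0.80 = 85. Check: 85 × 0.80 = 68 exactly.

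**What 82 recruits deliver**

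- Expected completers at 20% attrition: 82 × 0.80 = 65.6, that is 65 or 66.
- Shortfall against 68: 2 to 3.
- Largest loss that still leaves 68: 82 − 68 = 14, and 14 / 82 = 17.1%.

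**Effect on power**

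The article does not give the covariate correlation, the allocation ratio, the sidedness of the test or the metric of the effect size. The relative loss can be found without them. Take as given that 68 gives 80% power. At a fixed effect and a fixed allocation ratio, the expected test statistic scales with the square root of the sample size. With a two-sided 0.05 test (an assumption) and the normal approximation:

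- At 68, the expected statistic is 1.960 + 0.842 = 2.802, by construction.
- At 66, it is 2.802 × √(66/68) = 2.760, so power = Φ(2.760 − 1.960) = 78.8%.
- At 65, it is 2.802 × √(65/68) = 2.739, so power = Φ(2.739 − 1.960) = 78.2%.

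A direct ANCOVA calculation agrees. It assumes a standardized mean difference of 0.5, two-sided 0.05, equal groups, and a baseline-outcome correlation of 0.689, chosen so that 68 gives 80%.

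| Completers (split) | Power |
|---|---|
| 68 (34/34) | 80.0% |
| 66 (33/33) | 78.8% |
| 65 (33/32) | 78.2% |

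With a correlation of 0.685 instead, the three values are 79.6%, 78.4% and 77.7%. The loss is one to two percentage points either way.

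**The case against.** The arithmetic itself is not open to dispute; the case on the other side concerns its weight.

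- **Size.** The loss is one to two points of power, no analysis in the Statistical Analysis Plan section changes, and the 20% is itself a planning guess. A target that tolerates 17.1% is close to what was intended. This stands: the effect is small.
- **65 or 66.** Twenty per cent of 82 is 16.4 people. Losing 16 leaves 66, and reaching 65 means losing 17, which is 20.7%. This is fair, so a range of 65 to 66 is given here. Both values are below 68.
- **The power figure.** The article does not state the correlation, allocation or sidedness, so 78% cannot be derived from it. Participants join the waitlist only when a clinician is not available (Study Design), so equal groups are not assured. At a correlation of 0.685, even the full 68 split 45/23 would have about 75% power. This limits what 78% means: it is not an estimate of this trial's power. It does not affect the relative loss, because any assumptions that give 80% at 68 give about 78 to 79% at 65 to 66 with the same allocation ratio.

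The error is not a product of condensing the full protocol into an article, since all three figures are printed. Reading 68 as a number enrolled does not help either, because no attrition adjustment would then be needed.

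**Conclusion.** The concern holds. The recruitment target does not follow from the stated requirement and attrition rate: it should be 85, and 82 is three short. Under the plan's own 20% attrition, the trial ends with 65 to 66 completers and, if 68 is right for 80% power, with about 78 to 79%. The arithmetic conclusion rests only on the printed figures. The power figure also assumes a two-sided test and an unchanged allocation ratio, and takes the 68 as given without endorsing how it was reached. The error should be corrected because it is a published design figure that fails on its own terms, but it does not threaten the trial.

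**What to change.** Amend the attrition sentence in Sample Size in one of three ways:

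1. Keep 82 and state that it allows for 17% attrition (14 of 82). This costs one sentence and no participants, and needs no power figure.
2. Keep 82 and 20%, and state that 65 to 66 completers are expected, with power of about 78% if 68 would give 80%. This also costs one sentence, but the assumptions behind the power figure should be printed with it.
3. Keep 20% and recruit 85, changing the 82 in both Sample Size and the Abstract. This costs three more participants, at a clinic that reports about 20 relevant referrals a month (Recruitment and Informed Consent).

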#### Telephone Screening and Study Visits

Women who are interested in participating will receive an initial telephone screen to ensure eligibility. Following informed consent, participants deemed eligible will be enrolled into the study and complete their baseline assessment consisting of a structured clinical interview (Mini International Neuropsychiatric Interview for DSM-5 and the Sexual Disorders Module of the Diagnostic and Research Tool for DSM-5) and self-report measures. Upon confirming eligibility at the baseline assessment, participants will be assigned to a treating clinician to undergo four weekly sessions (up to 90 min) of individual CBT-SC-Peri. If a treating clinician is not immediately available, participants will be placed on a waitlist for 4 weeks before starting treatment. Participants who are on the waitlist for treatment will be asked to complete the self-report measures following the waitlist period/before starting treatment. To reduce attrition, participants will be compensated with a $20 gift card following each assessment visit at baseline, post-waitlist (for those in the waitlist group), and post-treatment, in addition to travel reimbursement via the form of a parking pass or bus tickets (if an in-person visit is conducted).

Because of the short duration of the treatment and the sensitive nature of the topic (sexual concerns), there may be an unintended effect of the study namely, no improvement or worsening of symptoms. Should this occur, the research participant will be offered further care by our treatment team within the WHCC, a clinic that is equipped with a multidisciplinary team including psychiatrists, obstetricians-gynecologists, and psychologists.

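### The planned two-time-point repeated measures ANCOVA, in its classical form, leaves out about 16 of 82 women; inflating the sample protects power but not the validity of the non-randomised contrast

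*Protocol article*

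**What the plan says.** The Sample Size section takes an effect of 0.5 ("we estimate a medium effect size of 0.5 for our study") and states the requirement as "a study power set at 80%, 68 participants are required to conduct our study". It then allows for loss: "Adjusting our sample for a 20% attrition rate, we plan on recruiting 82 participants". The rate is a single overall figure, not split by condition.

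The Statistical Analysis Plan section fixes the model for primary and secondary outcomes: "A two (treatment vs. wait-list) by two (time: pre-treatment, post-treatment) repeated measures ANCOVA will be used to examine differences". On adjustment it says: "Covariates for all analyses will include age, current marital status, medication use at baseline, treatment delivery method, and baseline depression and anxiety severity". The outcome's own baseline score is not listed, except so far as depression and anxiety are themselves the outcome.

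Under Telephone Screening and Study Visits, a woman goes to the wait-list when no clinician is free, so the conditions are not randomised. The same section offers a $20 gift card at each assessment plus travel reimbursement, expressly to reduce attrition. It says of the wait-list: "Participants who are on the waitlist for treatment will be asked to complete the self-report measures following the waitlist period/before starting treatment". It also allows that "there may be an unintended effect of the study namely, no improvement or worsening of symptoms".

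**The concern.** The plan expects to lose one woman in five. Apart from the retention payments, its stated response is a larger N. The named model compares mean change between conditions and, run classically, needs both scores from each woman. Women lost before follow-up then contribute nothing, although their full baseline battery has been collected.

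A larger N replaces the count but not the women who left. If the women who remain in CBT differ at baseline from those placed there, and the wait-list is not selected in the same way, regression towards the mean no longer cancels between groups. If women leave because of how they are responding, the remaining women's mean change misstates that of all women placed in the condition. Either way the efficacy contrast is affected, in a comparison that already lacks randomisation.

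Different loss patterns are plausible. Before the second score, a CBT woman attends up to four sessions of up to 90 minutes with homework, while a wait-list woman completes questionnaires just before the treatment she is waiting for. The article does not say that loss will differ.

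**Working it through.** **1. The plan's own figures.** Inputs from Sample Size: 68 evaluable, 20% attrition, 82 recruited.
- Expected loss: 82 x 0.20 = 16.4 women. Expected with both scores: 82 x 0.80 = 65.6, against 68 required.
- 82 is reproduced by 68 x 1.20 = 81.6. Dividing by the retention rate gives 68 / 0.80 = 85. So even the count is not quite restored, although the shortfall is only two to three women.

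**2. What the model estimates.** With two time points, the condition-by-time test is a difference in mean change (post minus pre) among women with both scores, adjusted for the listed covariates.

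**3. Loss related to the baseline score.** Assumptions, none of them in the documents: pre and post scores have SD 1 and correlation r; CBT loss is logistic in the baseline score with a log-odds slope of 1 per SD; wait-list loss is random; the covariates explain none of the loss. Let m be the absolute shift, in SD, of the mean baseline score of retained CBT women from that of all CBT women. Expected change falls by (1 - r) for each SD of baseline, so

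absolute bias = (1 - r) x m.

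Numerical integration gives m = 0.173 at 20% CBT loss and 0.253 at 30%.

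| CBT loss | r = 0.3 | r = 0.5 | r = 0.7 |
|---|---|---|---|
| 20% | 0.7 x 0.173 = 0.12 | 0.5 x 0.173 = 0.09 | 0.3 x 0.173 = 0.05 |
| 30% | 0.7 x 0.253 = 0.18 | 0.5 x 0.253 = 0.13 | 0.3 x 0.253 = 0.08 |

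The range is 0.05 to 0.18 SD, or 10% to about 35% of the planned 0.5. Random wait-list loss adds no bias, so the 20% row holds even if both conditions lose 20%: what matters is the pattern of loss, not only its rate. With a weaker slope of 0.5 at 30% loss the figures are 0.10, 0.07 and 0.04.

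On a scale where higher is better, loss of the lowest scorers understates the CBT effect and loss of the highest scorers overstates it.

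**4. Same mechanism in both conditions.** In a separate simulation (r = 0.68, driver correlated 0.5 with loss), baseline-related loss of 25/15% to 30/10% (CBT/wait-list) gave 0.025 to 0.05 SD for the change contrast. It gave about 0 when the baseline score was a covariate.

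**5. Loss related to the unseen outcome.** In the same simulation the bias was +0.056 at 25/15%, +0.11 at 30/10% and -0.11 at 10/30%. Equal 20/20% loss acting identically in both conditions gave about 0.

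**6. When nothing goes wrong.** Loss completely at random gave about 0 at 20/20, 25/15 and 30/10%.

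**7. What a likelihood analysis with all baseline scores achieves.** In the setting of step 3 its bias is about 0 (at most 0.005). If 30% CBT loss depends instead on the unseen change (log-odds slope 1 per SD, r = 0.5), the complete-case bias of 0.25 to 0.26 SD falls only to 0.19 to 0.20. It corrects the part that observed scores explain, and no more.

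**The case against.** The strongest reply is that the article names a model, not a missing-data policy. It nowhere says that women without a second score are dropped. A 2 x 2 repeated measures ANCOVA can be run on imputed data, and analysis sets and imputation are commonly left to a fuller document that is not shown. This stands so far as it goes: deletion is inferred from the classical form of the model, and the absence of a missing-data section is not the complaint. The complaint is that the article fixes a model that does not naturally use partial records in a trial forecasting 20% loss, when one that does is readily available.

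Four stronger readings are tempting, and the documents do not support them.
- Attrition is met only by over-recruiting. It is not: gift cards and travel reimbursement are offered, and virtual visits may also help. Only the statistical handling rests on N.
- Uneven loss in itself biases the contrast. It does not: random loss at 30/10% gave none.
- CBT women will leave more often, or leave because they did not benefit. Attrition is one overall figure, and the sentence on non-response or worsening introduces an offer of further care, not a forecast of drop-out.
- The effect will be overstated. The sign depends on who leaves.

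It is also fair that the illustrated sizes depend on the chosen slope, correlation and loss rates, and that the calculations leave out the six planned covariates. Baseline depression and anxiety could absorb part of any baseline-related selection. For those two outcomes the baseline score is in effect already adjusted for. For sexual function, desire, body image, relationship satisfaction and vasomotor symptoms it is not.

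**Conclusion.** The point holds as a weakness of the stated method, not as a demonstrated bias. In its classical form the planned ANCOVA sets aside about 16 of 82 women with baseline data, and inflating N does not address selective loss. In this non-randomised comparison, loss related to baseline or outcome that differs in pattern between conditions can bias the change contrast. Under the stated assumptions (20-30% baseline-related CBT loss at slope 1 per SD, random wait-list loss, r from 0.3 to 0.7, no covariate adjustment) the bias is 0.05 to 0.18 SD on a planned 0.5. Weaker selection gives less, and random loss gives none. The documents fix neither the size nor the sign. It is worth correcting because the remedy is cheap; confidence is moderate.

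**What to change.** In the Statistical Analysis Plan section, replace the repeated measures ANCOVA with a linear mixed model for repeated measures:
- fit it to all women placed in CBT or wait-list, each kept in the condition in which she was placed;
- take baseline and follow-up scores both as responses, so that a woman with only a baseline score contributes;
- leave baseline means free to differ by condition, since allocation is not random;
- keep the same covariates, entered with time interactions so that they adjust the change as they would in the ANCOVA;
- test condition by time.

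Report loss by condition. Because the mixed model corrects only loss explained by observed scores, add one sensitivity analysis that imputes missing CBT follow-up scores from the wait-list change.

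The cost is revised wording and a little more programming, with no extra women, visits or data. The downside is that the sensitivity estimate may be less favourable to CBT.
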